#### 2.2.4. Study Population and Inclusion Criteria

This clinical study will include people who (i) are between 20 and 60 years of age, (ii) have an omnivorous diet, (iii) have a body mass index greater than 18 kg/m^2^, and (iv) have given written consent. The exclusion criteria are as follows: (i) a smoking addiction, (ii) a known food allergy/intolerance, (iii) an inability to consume dairy or solid products, (iv) a high risk of infective endocarditis, (v) chronic pathologies, (vi) antibiotic treatment during the month preceding the start of the study, (vii) pregnancy in progress, parturient, or breast feeding, (viii) deprivation of liberty by judicial or administrative decision, (ix) psychiatric care, (x) legal protection (guardianship, trusteeship), (xi) having less than 20 natural teeth, with active cavities, (xii) performing mouthwashes or interdental hygiene regularly, and (xiii) using orthodontic braces.

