#### 2.2.3. Outcomes

The primary outcome will be to compare the number of total bacteria and periodontal pathogens of the interdental microbiota before (T0) and after 3 months (T2) of consumption of a diet enriched in cereal (einkorn) and reduced in meat.

The secondary outcomes will be as follows:-To compare the number of total bacteria and periodontal pathogens of the interdental microbiota before (T0) and after 1 month (T1) of consumption of a diet enriched in einkorn and reduced in meat.-To compare periodontal and oral clinical parameters before (T0), during (T1), and after (T2) the introduction of einkorn into the diet.-To compare general health indicators before (T0), during (T1), and after (T2) the introduction of einkorn into the diet through a consultation and a general medical examination.-To compare quality of life before (T0), during (T1), and after (T2) the introduction of einkorn into the diet through answers to a questionnaire.

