#### 2.2.7. A Description of the Procedure and Data Collection

The participants will have to change their diet for 3 months. They will reduce their meat consumption by half and will consume einkorn (at least 100 g/day of cooked whole grains, 6 days/week). To achieve this, cooking workshops will be offered during the 3 months of the study.

Three visits will be planned during the study, (T0 (inclusion), T1 (1 month after T0), and T2 (2 months after T1)), to collect the following data:-Microbiological: Sampling of interdental microbiota [54,55,56,57] and real-time PCR to quantify the total number of bacteria and 9 periodontal bacteria. Among them, several are considered cancer risk factors: *Aggregatibacter actinomycetemcomitans*, *Porphyromonas gingivalis*, *Tannerella forsythia*, *Treponema denticola*, *Prevotella intermedia*, *Parvimonas micra*, *Fusobacterium nucleatum*, *Campilobacter rectus*, and *Eikenella corrodens*.-Oral health: Quantitative and qualitative analysis of saliva (GC saliva check buffer, GC, Sucy-en-Brie, France) and measurement of periodontal parameters (Bleeding On Probing (BOP) [58], Gingivitis Index (GI) [59], Plaque Index (PI) [60], Clinical Attachment Level (CAL), and Probing Pocket Depth (PPD) [61].-General health: Body Mass Index (BMI), blood pressure, and abdominal circumference.-Quality of life: MOS SF-36 self-questionnaire validated in French [62].

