#### 2.2.8. Data Analysis

Quantitative data encompassing the entire population will be described, including measures of central tendency and dispersion such as mean, standard deviation, and median. Qualitative variables will be summarized, detailing frequencies and percentages for each level, accounting for missing values without including them in frequency calculations. Absolute and relative frequencies will be calculated for the entire population and at multiple time points (T0, T1, T2). A linear regression analysis will assess the relationship between the interdental microbiome and oral and general health indicators. Paired *t*-tests will compare relative amounts of total and pathogenic bacteria between T0, T1, and T2. Statistical significance will be set at α = 0.05. The analysis of health indices, anthropometric measures, health parameters, and quality of life will employ analysis of variance (ANOVA) to compare trends over time. Linear mixed models could evaluate the impact of dietary intervention on the interdental microbiome, treating time as a random variable and covariates as fixed variables.

Intention-to-treat analyses will be performed on imputed data from all randomized patients using multiple imputation by chained equations, based on a chained Monte-Carlo–Markov algorithm under the assumption of missing data at random.

Descriptive statistics will be calculated with SPSS 12.0 (SPSS Inc., Chicago, IL, USA). Statistical tests (*p*-values) will be calculated with SUDAAN 7.0 (Research Triangle Institute, Research Triangle Park, NC, USA) for repeated measurements (measurements throughout the follow-up period).

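### Regular einkorn eaters are not excluded, although three secondary outcomes treat T0 as the point before einkorn enters the diet

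*Protocol article*

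**What the plan says.** Section 2.2.4 of the protocol article lists four inclusion and thirteen exclusion criteria for the clinical study. The one that concerns habitual diet is to "have an omnivorous diet". The food-related exclusions are "a known food allergy/intolerance, (iii) an inability to consume dairy or solid products". These concern whether a person can eat certain foods, not what the person eats now.

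Section 2.2.7 defines the intervention: "They will reduce their meat consumption by half and will consume einkorn (at least 100 g/day of cooked whole grains, 6 days/week". The meat part is relative to the person's own habit. The einkorn part is a fixed minimum, the same for everyone.

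Section 2.2.3 states the primary comparison as "before (T0) and after 3 months (T2) of consumption of a diet enriched in cereal (einkorn) and reduced in meat". Three secondary outcomes (periodontal and oral parameters, general health indicators, quality of life) are instead worded as "before (T0), during (T1), and after (T2) the introduction of einkorn into the diet".

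Section 2.2.1 describes a single-arm design, and section 2.2.8 says paired t-tests "will compare relative amounts of total and pathogenic bacteria between T0, T1, and T2".

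**The concern.** With no control arm, the only source of signal is the change within each person between T0 and T2. That change is informative about einkorn only if T0 precedes regular einkorn consumption. The outcome wording takes this for granted, but the eligibility list does not secure it.

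A person who already eats einkorn regularly meets every dietary criterion. For that person the three secondary outcomes do not describe what is measured, and the added einkorn is less than for a newcomer. The data listed in section 2.2.7 (microbiology, oral health, general health, SF-36) do not include einkorn or meat intake. On the article's account, such participants could therefore not be identified afterwards. Section 3 names non-adherence as a limitation but does not mention baseline diet. It also makes the follow-on three-arm randomized trial depend on this pilot giving significant results, so an avoidable loss of contrast would matter.

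**Working it through.** **1. Who has how much change.** The fixed minimum is 100 g × 6 days = 600 g of cooked einkorn per week. For a participant already eating e grams per week, the instruction requires at least max(0, 600 − e) more. The values of e below are illustrations, since the article gives no baseline intakes.

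- e = 0: at least 600 g/week added.
- e = 200: at least 400 g/week added.
- e = 600: nothing further required.

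In all three cases meat is still halved. An adherent participant who eats meat therefore always has some change. A near-zero change needs both a very low meat intake and einkorn use already near the minimum.

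**2. The plan's own sample size.** Section 2.2.6 gives 90% power, a difference of 0.5, 36 evaluable and 40 included with 10% dropout. Section 2.2.8 gives paired t-tests and "Statistical significance will be set at α = 0.05". The SD of the paired difference and the sidedness are not stated. I assume SD = 1, so the standardized difference is 0.5.

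- One-sided, normal approximation: n = ((1.645 + 1.282)/0.5)² = 34.3, so 35. With the noncentral t, n = 36 and power at 36 is 90.3%. This reproduces.
- Two-sided, noncentral t: n = 44, and power at 36 is 83.1%. This does not reproduce unless the SD is about 0.89.
- Dropout: 36/(1 − 0.10) = 40. This reproduces.

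**3. Sensitivity to a smaller contrast.** Let a share f of participants obtain only a fraction r of the full effect. The mean effect is then 0.5 × (1 − f(1 − r)). Neither f nor r is in the article, so both are assumptions. Setting r = 0 gives an upper bound on the loss for each f. With n = 36 and SD = 1:

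| f (r = 0) | Mean effect | Power, one-sided | Power, two-sided |
|---|---|---|---|
| 0% | 0.50 | 90.3% | 83.1% |
| 10% | 0.45 | 84.2% | 74.7% |
| 20% | 0.40 | 76.1% | 64.6% |
| 30% | 0.35 | 66.1% | 53.3% |

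If affected participants keep half the effect (r = 0.5), the share needed for the same loss doubles. For example, f = 20% gives 0.5 × (1 − 0.20 × 0.5) = 0.45, which is the 10% row.

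The table shows how little reserve 36 has. It does not estimate the loss in this study.

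**The case against.** A reader might infer that some participants will have no diet change and that the T0–T2 result is therefore diluted by a known amount. The documents do not support this, for four reasons.

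- Only the meat component is relative. A light meat eater who is new to einkorn still adds the full weekly minimum, and a current einkorn eater still halves meat.
- No share of affected participants is given. Nothing in section 2.2.5 suggests that it is large: recruitment is from the laboratory's volunteer database, an email to hospital staff and the laboratory's social networks. Customers of farmer-bakers, arguably the likeliest einkorn eaters, are sought for the behavioral study. The Introduction itself calls the ancient wheats less common.
- The expected difference of 0.5 may already be an average over omnivores as they would be enrolled. In that case nothing is lost relative to the plan.
- The primary outcome speaks of a diet enriched in einkorn, which remains true for someone who already eats some.

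A second inference would be that a minimum meat intake is needed because halving is relative. Two people eating meat 2 and 14 times a week would drop 1 and 7 occasions, a 7-fold range. These eaters are invented, and the range ignores the einkorn component they share. Section 2.2 places the question in the general population, and varied meat intake is part of that population. A floor would answer a narrower question.

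It can also be said that a full protocol may hold finer screening rules. That is possible. But the article itemizes eligibility down to guardianship and orthodontic braces, and the dietary criterion as stated does not match the outcome wording.

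What stands after all this is the mismatch between the eligibility list and the three secondary outcomes.

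**Conclusion.** The point holds in a limited form. As written, eligibility admits regular einkorn consumers. For them the before-introduction baseline in three secondary outcomes does not exist, and the within-person contrast that the single-arm design depends on is reduced, though not to zero. The number affected is unknown and may be small. The power figures are conditional on assumed shares, an SD of 1 and, for reproducing 36, a one-sided test.

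This is a cheap improvement that brings eligibility into line with the outcomes. It does not show that the study cannot answer its question. The variation in meat contrast between participants is real, but it is a consequence of a defensible design choice.

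**What to change.** Add one exclusion criterion to section 2.2.4: *regular einkorn consumption before T0*. The investigators should define what counts as regular and how far back to look, because the article offers no basis for either. One screening question at the inclusion visit is enough to check it.

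The cost is a marginally smaller recruitment pool and one line of amendment. Visits, procedures and analysis do not change.

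A minimum habitual meat intake may be considered if the investigators want a more uniform contrast in meat. They should weigh it against the narrowing of the general-population question.

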#### 2.2.5. Sample Methodology

Participants will be recruited using (i) a database of volunteers who have already participated in other studies for the P2S laboratory and who have indicated their wish to participate in other similar studies, (ii) a call for participation by an email sent to all HCL staff, and (iii) a call for participation broadcast on the social networks of the P2S laboratory.

#### 2.2.6. Sample Size

The research hypothesis is part of a superiority test (fewer pathogenic bacteria after changing diet versus before). Referring to the results obtained by Bourgeois et al. [53], with a statistical power of 90% and an expected reduction difference at 3 months of 0.5, 36 participants must be included for significance with a *p*-value < 0.05. Considering an estimated dropout rate of 10%, we plan to include 40 participants. If there are larger dropouts or exclusions, recruitment of additional volunteers will be implemented to ensure the inclusion of 36 participants.

#### 2.2.7. A Description of the Procedure and Data Collection

The participants will have to change their diet for 3 months. They will reduce their meat consumption by half and will consume einkorn (at least 100 g/day of cooked whole grains, 6 days/week). To achieve this, cooking workshops will be offered during the 3 months of the study.

Three visits will be planned during the study, (T0 (inclusion), T1 (1 month after T0), and T2 (2 months after T1)), to collect the following data:-Microbiological: Sampling of interdental microbiota [54,55,56,57] and real-time PCR to quantify the total number of bacteria and 9 periodontal bacteria. Among them, several are considered cancer risk factors: *Aggregatibacter actinomycetemcomitans*, *Porphyromonas gingivalis*, *Tannerella forsythia*, *Treponema denticola*, *Prevotella intermedia*, *Parvimonas micra*, *Fusobacterium nucleatum*, *Campilobacter rectus*, and *Eikenella corrodens*.-Oral health: Quantitative and qualitative analysis of saliva (GC saliva check buffer, GC, Sucy-en-Brie, France) and measurement of periodontal parameters (Bleeding On Probing (BOP) [58], Gingivitis Index (GI) [59], Plaque Index (PI) [60], Clinical Attachment Level (CAL), and Probing Pocket Depth (PPD) [61].-General health: Body Mass Index (BMI), blood pressure, and abdominal circumference.-Quality of life: MOS SF-36 self-questionnaire validated in French [62].

#### 2.2.8. Data Analysis

Quantitative data encompassing the entire population will be described, including measures of central tendency and dispersion such as mean, standard deviation, and median. Qualitative variables will be summarized, detailing frequencies and percentages for each level, accounting for missing values without including them in frequency calculations. Absolute and relative frequencies will be calculated for the entire population and at multiple time points (T0, T1, T2). A linear regression analysis will assess the relationship between the interdental microbiome and oral and general health indicators. Paired *t*-tests will compare relative amounts of total and pathogenic bacteria between T0, T1, and T2. Statistical significance will be set at α = 0.05. The analysis of health indices, anthropometric measures, health parameters, and quality of life will employ analysis of variance (ANOVA) to compare trends over time. Linear mixed models could evaluate the impact of dietary intervention on the interdental microbiome, treating time as a random variable and covariates as fixed variables.

Intention-to-treat analyses will be performed on imputed data from all randomized patients using multiple imputation by chained equations, based on a chained Monte-Carlo–Markov algorithm under the assumption of missing data at random.

Descriptive statistics will be calculated with SPSS 12.0 (SPSS Inc., Chicago, IL, USA). Statistical tests (*p*-values) will be calculated with SUDAAN 7.0 (Research Triangle Institute, Research Triangle Park, NC, USA) for repeated measurements (measurements throughout the follow-up period).

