### 2.2. Evaluation of the Impact of the Planetary Health Diet on Interdental Microbiota Dysbiosis, a Risk Factor of NCDs Such as Cancer, and on Quality of Life in the General Population (Clinical Study)

#### 2.2.1. Study Design

The “clinical study” will be a single-arm longitudinal comparative pilot study (Figure 3). The protocol will follow the Standard Protocol Items: recommendations for international trials (SPIRIT) [52].

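### The optional mixed model makes time random, so it has no fixed-effect estimate, confidence interval or test of the T0–T2 change it is meant to evaluate

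*Protocol article*

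**What the plan says.** All from the protocol article, clinical study:

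- Section 2.2.1: the study "will be a single-arm longitudinal comparative pilot study". There is no control group.
- Section 2.2.3: the primary outcome is to "compare the number of total bacteria and periodontal pathogens of the interdental microbiota before (T0) and after 3 months (T2"). The T0–T1 comparison is secondary.
- Section 2.2.7: "Three visits will be planned during the study, (T0 (inclusion), T1 (1 month after T0), and T2 (2 months after T1")), so time has three levels.
- Section 2.2.8, on the main test, which is a paired t-test: "tests will compare relative amounts of total and pathogenic bacteria between T0, T1, and T2".
- Section 2.2.8, on the mixed model: "Linear mixed models could evaluate the impact of dietary intervention on the interdental microbiome", and then "treating time as a random variable and covariates as fixed variables".

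No sentence adds a fixed time term to the mixed model.

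**The concern.** In a mixed model the quantity to be estimated and tested belongs in the fixed part. The random part describes variation across units regarded as draws from a population, here the participants. In a one-arm before-after study every participant follows the diet, so its effect can appear only as a difference between visits. The stated model puts visit in the random part and leaves only covariates fixed. Those three visits are not a sample from a population of visits; they are the conditions the study sets out to compare.

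This matters because it is the only model in Section 2.2.8 that would give a diet effect adjusted for covariates. The linear regression named there relates the microbiome to health indicators and does not estimate the change on diet. Section 3 itself says that oral hygiene and physical activity may influence the oral microbiota, so an adjusted analysis is likely to be wanted. Run as written, it would report no T2–T0 effect, or would place a smaller predicted change beside the paired t-test with no stated basis for inference.

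**Working it through.** **1. The plan's own figure.** Section 2.2.6 gives power 90%, difference 0.5, p < 0.05, 36 participants, and 40 after 10% dropout. It states neither an SD nor the sidedness. Assume an SD of the paired difference of 1.

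- One-sided, normal approximation: n = ((1.645 + 1.282)/0.5)² = 34.3, so 35. With the t distribution: 35.7, so **36**, which matches. Power at 36 is 90.3%.
- Two-sided, t distribution: 44, no match; power at 36 is 83.1%. Two-sided testing returns 36 only if the SD of the difference is about 0.90.
- Dropout: 36/(1 − 0.10) = **40**, which matches.

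The design figure is thus consistent with a paired comparison and does not depend on the mixed model.

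**2. The model as written.** For participant i at visit j:

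y_ij = β₀ + x_i′γ + (participant term, if any) + τ_j + e_ij, with τ_j ~ N(0, σ²_τ) and j = T0, T1, T2.

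The fixed parameters are β₀ and γ. With baseline covariates, the model's expected T2–T0 change is zero by construction. Time enters only through σ²_τ, estimated from three levels. A test of σ²_τ = 0 asks whether the visits differ at all. It has no direction and does not isolate T2 against T0, whereas Section 2.2.6 states a directional hypothesis.

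**3. What can still be extracted.** With balanced data the predicted contrast is λ × (mean at T2 − mean at T0), where λ = σ²_τ / (σ²_τ + σ²_e/n). For illustration take n = 36 and visit means 0, −0.25 and −0.5. The variance of the three means is (0.25² + 0 + 0.25²)/2 = 0.0625.

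| Assumption | σ²_τ | σ²_e/n | λ | Predicted T2–T0 (true −0.5) |
|---|---|---|---|---|
| Participant random; SD of difference 1, so σ²_e = 1²/2 = 0.5 | 0.0625 | 0.0139 | 0.82 | −0.41 |
| Participant random; SD of difference 0.90, so σ²_e = 0.81/2 = 0.405 | 0.0625 | 0.0113 | 0.85 | −0.42 |
| No participant term; SD 1 per visit, within-person correlation 0.5 | 0.0625 + (0.5 − 1.0)/36 = 0.0486 | 1/36 = 0.0278 | 0.64 | −0.32 |

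These plug in expected values. Simulation also carries the uncertainty in σ²_τ:

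- 150 data sets, participant random: mean observed difference −0.52, mean predicted −0.42 (0.42/0.52 = 0.81, so 19% smaller); mean λ 0.75; σ²_τ estimated as exactly zero in 4%.
- 20,000 data sets, true change −0.50: mean predicted about −0.39 with a participant term (σ²_τ zero in about 3%) and −0.30 without one (zero in about 11%).

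When σ²_τ is estimated as zero, the predicted change is zero whatever the visit means show.

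**4. One simulated data set, three specifications (true T2–T0 = −0.5).**

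| Specification | What is reported |
|---|---|
| Visit fixed, participant random | T2–T0 = −0.514, SE 0.175, 95% CI −0.857 to −0.170, p = 0.003 |
| Time and participant random, no fixed time | Intercept −0.234; time variance 0.075 (SE 0.123); no T2–T0 coefficient, CI or p-value |
| Random time slope within participant, no fixed slope | Intercept −0.292; slope variance 0.011; no T2–T0 coefficient; convergence warnings |

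Only the first specification answers the study question directly.

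**The case against.** **The model is optional and the main test stands.** This is the strongest objection, and it is correct. The mixed model is introduced with *could*, whereas the paired t-tests are introduced with *will*. Those tests estimate and test the within-person T0–T2 change. A reader might infer that the primary comparison cannot be made or that pairing is lost; the article does not support that. The objection lowers the severity but leaves the wording of the model wrong.

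**A random slope on top of a fixed time effect may have been meant.** That would be a sensible model. The text does not describe it, because it lists only covariates as fixed.

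**A condensed article leaves model detail to the full plan.** For this reason the failure to name participant as the grouping factor is not held against the plan. The assignment of time to the random part is different: it is a stated specification, and it is wrong for the stated purpose.

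**The shrinkage figures depend on assumptions.** They do. SD, correlation and the T1 mean are not in the article, and whether a participant term is included changes the result. The figures illustrate direction and order of size only. The absence of a fixed T2–T0 parameter depends on none of them.

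**The secondary outcomes.** The article says their analysis "will employ analysis of variance (ANOVA) to compare trends over time", and a reader might infer a one-way ANOVA that ignores pairing. The closing paragraph of Section 2.2.8 says p-values will be computed with software for repeated measurements, so that reading is not supported and no point is made of it.

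**Conclusion.** The point holds, at moderate severity. As written, the mixed model in Section 2.2.8 has no fixed-effect estimate, confidence interval or test of T2–T0. This follows from the single-arm design and the stated roles of time and covariates, and needs no numerical assumption. To say that the model gives no estimate of any kind would go too far, since a shrunken prediction can be extracted. Under the assumptions above that prediction falls short of a true change of 0.5 by about 15% (λ = 0.85) to 40% (−0.30 against −0.50), and in some data sets it is exactly zero.

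The paired T0–T2 comparison and the 36/40 sample size are unaffected. What is compromised is the only model offered for a covariate-adjusted diet effect, should it be used.

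**What to change.** Replace the clause on the roles of time and covariates in Section 2.2.8. Suggested content: if a linear mixed model is used, visit (T0, T1, T2) enters as a categorical fixed effect, participant as a random intercept, and covariates as fixed effects; the T2–T0 contrast (matching the primary outcome) and the T1–T0 contrast (matching the secondary one) are reported with 95% confidence intervals. If person-to-person variation in response over time is also of interest, a random time term may be added to the fixed visit effect but must not replace it.

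The cost is one sentence. No new data, visits or participants are needed, and the paired t-tests stay as planned.
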